### Outcome parameters

The outcome parameters are tumour free margins (and number of re-excisions), resection specimen volume, cosmetic outcome, quality of life, cost effectiveness also participating physicians will score the difficulty of the procedures. Patients will be asked to fill in questionnaires on pain during the procedure, quality of life and the cosmetic outcome. A specific burden questionnaire, aimed at evaluating the burden of the cosmetic result, is developed. Such an instrument is currently not available. To further assess the net impact in terms of Health Related Quality of Life (HRQoL) also the EQ5D and the EQVAS will be obtained at T = 0, 6, 12 and 26 weeks after the initial diagnostic work-up.

The outcome of the study can be divided in 3 groups of outcome; negative outcomes, outcomes open to discussion and positive outcomes.

Less tumour free margins in the ROLL group are considered negative outcomes, also more tumour free margins in combination with a larger resection volume is a negative outcome and equal tumour free resection margins combined with larger resection specimens are considered negative. Secondly outcomes open to discussion are more tumour free margins in combination with an equal resection volume and equal resection margins in combination with smaller resection specimens in the ROLL group. Finally positive outcomes are more tumour free resection margins in combination with smaller resection specimens and equal tumour free margins in combination with smaller resection specimens. These data will be based on pathology reports. All surgical specimens will be analysed by one dedicated reference pathologist ([name]).

The overall outcome will be cost-effectiveness in terms of incremental costs per quality adjusted life years gained with a 6 month time horizon. We hypothesize that the short-term burden will result in an overall superior result after ROLL.

When indeed our expectations are evidenced, than a situation of dominance may occur, i.e., costs may be saved while at the same time clinical effects are optimal after ROLL.

Should the results indicate that overall the WGL procedure leads to better clinical outcome a cost-effectiveness analysis is foreseen using bootstrapping to assess the uncertainty with regard to the balance between costs and effects. All analyses will be limited to a half year time horizon. Accordingly, discounting of costs or effects is not applicable.

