### Statistical analysis

The difference in radicality of the resected specimen in both groups will be calculated in a confidence interval (CI) of 95%.

The volume of the specimens is presented in mm^3 ^and the maximum diameter in mm. The approach for the cost-analysis is comparing actual costs incurred with both strategies up until 6 months after the first operation. Costs estimates will be based on the actual costs of both procedures. This includes the costs of operation rooms, hospital stay, ultrasound/stereotactic imaging, wire placement, gamma probe use and if necessary, costs associated with complications and re-operations.

The degree of difficulty of radiological and surgical procedure will be expressed on a 1–10 scale (1 being extremely easy and 10 extremely difficult). The average score for both procedures will be calculated. Patient discomfort of the radiological procedure is expressed on 1–10 scale to (1 being not painful and 10 being very painful).

The success rate of the sentinel node procedure is presented in a percentage of successfully detected and found sentinel nodes.

The weight and size of the surgical specimens as well as the degree of difficulty of the surgical and radiological procedures and patients discomfort in both groups will be analyzed using the students T test.

The cost-effectiveness analysis will be done using the multivariate analysis. If the baseline characteristics differ after randomization, i.e. there is a lack of balance in the confounding factors, this will be corrected using the multivariate analysis.

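### Adjustment of the QALY difference for T = 0 EQ5D should be fixed in advance, not left to depend on an observed baseline imbalance

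*Protocol article*

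**What the plan says.** Under Outcome parameters, the protocol article sets the economic endpoint: "The overall outcome will be cost-effectiveness in terms of incremental costs per quality adjusted life years gained with a 6 month time horizon". The utility data come from the same section: "the EQ5D and the EQVAS will be obtained at T = 0, 6, 12 and 26 weeks after the initial diagnostic work-up". It gives no formula for turning these four measurements into QALYs.

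Under Statistical analysis, the method is one sentence: "The cost-effectiveness analysis will be done using the multivariate analysis". The next sentence is the only rule on baseline differences: "If the baseline characteristics differ after randomization, i.e. there is a lack of balance in the confounding factors", then "this will be corrected using the multivariate analysis". Neither sentence names a covariate, and neither says what counts as a difference.

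Bootstrapping appears under Outcome parameters, for the case in which WGL gives the better clinical result: "a cost-effectiveness analysis is foreseen using bootstrapping to assess the uncertainty with regard to the balance between costs and effects".

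**The concern.** Utility at T = 0 is not an ordinary baseline characteristic for this endpoint. Under the usual area-under-the-curve calculation it is a component of the 26-week QALY, and a patient's first EQ5D score is likely to be correlated with her later ones. It therefore explains part of the QALY variance whether or not the arm means happen to look alike.

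A rule that adjusts only after an imbalance has been seen has two costs here. When no imbalance is declared, the precision that the T = 0 score offers may be given up. And because no criterion is stated, the decision to adjust can be taken after the data are known. The QALY difference feeds the cost-per-QALY ratio and the dominance conclusion that the article anticipates. The expected ROLL advantage runs through short-term burden and may be small on the QALY scale, so precision matters.

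**Working it through.** The article gives no figure for the EQ5D, QALY or cost-effectiveness comparison, so there is nothing of the plan's own to reproduce. The check asks what fixed adjustment would be worth.

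**Inputs**
- From the article: EQ5D at weeks 0, 6, 12 and 26 (Outcome parameters); 158 patients per arm (Sample size).
- Assumed: trapezoidal QALY; EQ5D SD 0.20 at each visit (range 0.15 to 0.25); equal correlation ρ of 0.3, 0.5 or 0.7 between all visits; complete data.

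**Step 1: weights.** The intervals are 6, 6 and 14 weeks. Each visit takes half of each adjoining interval, giving 3, 6, 10 and 7 weeks (sum 26), divided by 52 for QALYs. T = 0 carries 3/26 = 11.5% of the weight.

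**Step 2: unadjusted standard error.** The squared weights sum to 9 + 36 + 100 + 49 = 194, and the cross-products to 26² − 194 = 482. So SE = 0.20 × √(194 + 482ρ)/52 × √(2/158).

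**Step 3: share of variance explained by T = 0.** The covariance of the QALY with T = 0 is proportional to 3 + 23ρ, so R² = (3 + 23ρ)²/(194 + 482ρ). The adjusted SE is the unadjusted SE × √(1 − R²).

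| ρ | 194 + 482ρ | SE unadjusted | R² | SE adjusted | Fall in SE |
|---|---|---|---|---|---|
| 0.3 | 338.6 | 0.0080 | 98.01/338.6 = 0.289 | 0.0067 | 16% |
| 0.5 | 435.0 | 0.0090 | 210.25/435.0 = 0.483 | 0.0065 | 28% |
| 0.7 | 531.4 | 0.0100 | 364.81/531.4 = 0.687 | 0.0056 | 44% |

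The percentage fall does not depend on the SD, which cancels. The SEs themselves scale with it: at ρ = 0.5 they go from 0.0068 to 0.0049 for SD 0.15, and from 0.0113 to 0.0081 for SD 0.25.

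**Step 4: a difference that nobody would flag.** One standard error of the T = 0 difference is 0.20 × √(2/158) = 0.0225, about half the 0.044 (1.96 × 0.0225) that a conventional two-sided 5% test would require. The associated shift in the unadjusted QALY difference is (3 + 23ρ)/52 × 0.0225 = 0.0043, 0.0063 or 0.0083. Only 3/52 × 0.0225 = 0.0013 of that comes through the T = 0 term itself; the rest comes through the assumed correlation with later visits.

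For scale only, a burden of 0.1 utility lasting 2 weeks is 0.1 × 2/52 = 0.0038 QALY. The article gives neither the size nor the duration of the burden, so this is an illustration, not an expected effect.

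**The case against.** A reader might infer that the QALY comparison is planned without adjustment and that baseline differences pass straight into the result. The article does not say that. It plans a multivariate analysis, and the sentence after it promises correction of imbalance; T = 0 EQ5D could be a covariate under either. It is neither included nor excluded. The covariate list and the QALY formula are details that a journal article commonly leaves to the full protocol or analysis plan, so their absence is no fault in itself.

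Nor is there bias in expectation. Under randomization a chance difference at T = 0 averages out, and a correct unadjusted interval already allows for it.

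It is also tempting to say that adjustment would secure the sign of the incremental QALY. It would not. With a true effect of 0.0038 QALY, the normal-approximation probability of a wrong-signed estimate is about 32%, 34% or 35% unadjusted and still 28%, 28% or 25% adjusted (ρ = 0.3, 0.5, 0.7).

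Finally, the endpoint is not the one that sets the sample size, which rests on tumour free margins, and the Economic evaluation section describes a cost comparison as the initial approach.

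All of this stands. What it leaves untouched is that the article is not silent on when baseline is corrected. It states a rule, the rule depends on what is observed, and for a baseline measure of the outcome itself a fixed rule is better.

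**Conclusion.** The point holds as a free improvement. For the cost-per-QALY outcome, the stated conditional rule, with no criterion, is weaker than adjustment for T = 0 EQ5D fixed in advance.

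The size is a fall of about 16% to 44% in the standard error of the QALY difference for between-visit correlations from 0.3 to 0.7. This rests on a trapezoidal QALY, equal correlations and variances across visits, and complete data from 158 patients per arm; none of these except the 158 is given in the article. The further benefit, removing a choice that could be made after seeing the data, needs no numerical assumption.

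The documents do not support saying that the planned comparison is unadjusted or biased, or that every patient will supply a T = 0 score. They say only that the questionnaire is to be obtained.

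**What to change.** For QALYs, replace the conditional rule with a fixed one:
- The between-arm QALY difference is always estimated by regression on arm and T = 0 EQ5D, whether or not the arms look different at baseline.
- This adjusted difference is used in the cost-per-QALY ratio and re-estimated in each bootstrap sample.
- T = 0 EQ5D is completed before the allocation is known. The article times T = 0 from the diagnostic work-up and does not place it relative to randomization; the covariate is safe only if it cannot be influenced by knowledge of the arm.

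The cost is a sentence or two in the analysis section. The questionnaire is already scheduled, and no patients or visits are added.

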### Randomization

Randomization is stratified for hospital. In each hospital, randomization within strata is blocked with a fixed block size. Randomization is performed by an independent trial center. If a patient meets the inclusion criteria and has provided informed consent, the physician contacts the trial center by phone. The trial center will perform the randomization of the patients.

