### Sample size

Sample size is calculated based on the primary endpoint: tumour free margins. Based on currently available literature we assume a difference in tumour free margins of 15% in favor of the ROLL procedure [8-14]. With a statistical power of 80% to detect this 15% improvement as significant (p < 0.05), we will require 158 patients in the control (WGL) group and 158 in the ROLL group.

Assuming a weight of 50 gr in the WGL group and a difference of 10 gr in the ROLL group [15] and a standard deviation of 3 gr, α = 0.05 and β = 0.80, the groups are sufficient to show a significant reduction in weight.

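### Covariate adjustment depends on observed baseline imbalance, so the model is data-dependent and hospital, the stratification factor, would almost never enter it

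*Protocol article*

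**What the plan says.** The rule closes the Statistical analysis section of the protocol article: "If the baseline characteristics differ after randomization, i.e. there is a lack of balance in the confounding factors, this will be corrected". The means of correction is a multivariate model. What counts as a difference is not defined, and no covariates are listed.

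The sentence directly before it reads "The cost-effectiveness analysis will be done using the multivariate analysis", so the rule may apply to cost-effectiveness only or to every outcome.

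Earlier in the same section the other comparisons are described without covariates. For margins, "The difference in radicality of the resected specimen in both groups will be calculated in a confidence interval (CI) of 95" per cent. For specimen weight and size, procedural difficulty and discomfort, the plan is a two-sample test: "patients discomfort in both groups will be analyzed using the students T test".

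The Randomization section says "Randomization is stratified for hospital", with fixed-size blocks within each hospital and allocation by an independent trial centre. Hospital is not named in any analysis. The Outcome parameters section schedules EQ-5D at T = 0, 6, 12 and 26 weeks from the initial diagnostic work-up.

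**The concern.** An independent centre allocates patients at random, so any baseline difference between arms is due to chance. It is not confounding in the usual sense, and its observed size says nothing about whether a variable predicts the outcome. A rule that selects on imbalance therefore selects on the wrong property: an irrelevant variable that happens to differ is adjusted for, and a strong predictor that happens to look balanced is left out.

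The rule also works against the design. Stratified blocks keep the arms nearly equal within each hospital, so hospital will hardly ever appear imbalanced, although it is the one covariate that the design itself singles out.

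At stake are precision and a fixed analysis. Because the trigger is undefined, someone must decide after seeing the data whether to adjust and for what.

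**Working it through.** **1. Context: the planned size.** "Sample size is calculated based on the primary endpoint: tumour free margins"; 80% power, p < 0.05, a 15% difference and 158 per arm are given there, but no control rate. Taking 15 percentage points and a two-sided test without continuity correction,

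n = [1.96·√(2p̄(1−p̄)) + 0.8416·√(p₁(1−p₁) + p₂(1−p₂))]² / (p₂−p₁)².

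For 58% against 73%, p̄ = 0.655 and n = (1.3176 + 0.5587)² / 0.0225 = 156.5, so 157. Control rates of 57%, 58% and 59% give 159, 157 and 155. With continuity correction, 62% to 64% gives 160 to 155. The planned size is attainable. The point here does not depend on it, but 58% against 73% is a reasonable scenario to simulate.

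**2. How often chance fires the trigger.** Assume k independent characteristics, each tested at 5%. The protocol gives neither k nor a threshold.

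- k = 5: 1 − 0.95⁵ = 0.226
- k = 10: 1 − 0.95¹⁰ = 0.401

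**3. What the rule does to power and error.** Simulation with 158 per arm, five independent covariates and 20,000 runs per scenario. The triggered rule adjusts only for covariates with baseline p < 0.05. For the binary outcome (58% against 73%) the estimate is an adjusted risk difference with robust standard error; the covariates together have SD 0.7 (moderate) or 1.2 (stronger) on the log-odds scale. For the continuous outcome the effect is 0.315 SD and the covariates explain R² = 0.1 or 0.3. All prognostic strengths are assumed.

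| Scenario | Power: unadjusted | Power: triggered | Power: pre-specified | Type I error: triggered |
|---|---|---|---|---|
| Binary, moderate | 80.8% | 81.0% | 83.8% | 0.047 |
| Binary, stronger | 80.9% | 81.7% | 87.8% | 0.042 |
| Continuous, R² 0.1 | 79.6% | 79.8% | 82.8% | 0.046 |
| Continuous, R² 0.3 | 79.2% | 80.3% | 90.9% | 0.044 |

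The Monte Carlo standard error at 0.05 is √(0.05 × 0.95 / 20,000) = 0.0015.

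- Binary: pre-specified adjustment gains 83.8 − 80.8 = 3.0 and 87.8 − 80.9 = 6.9 points. The triggered rule gains 0.3 and 0.8 (from 0.8077 to 0.8104, and from 0.8087 to 0.8170).
- Variance of the risk difference relative to unadjusted, stronger case: triggered (0.0519/0.0533)² = 0.95; pre-specified (0.0482/0.0533)² = 0.82.
- If the better of the unadjusted and the fully adjusted result is reported, type I error is 0.065 (R² 0.1) and 0.078 (R² 0.3) for the continuous outcome.

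**4. Hospital.** The simulated covariates are not balanced by design, so the table does not measure the hospital effect. That part is reasoning. Stratified blocks remove most between-hospital variation from the true sampling variance of the treatment difference, but an unadjusted standard error still counts it. If hospital explains a share h of the outcome variance, the unadjusted standard error is too large by about 1/√(1−h). The documents give no value for h; with h = 0 there is no loss.

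**5. QALYs.** If QALYs are computed as an area under the curve by trapezoids (an assumption), the T = 0 value carries half of the first 6 weeks, 3/52 = 0.058 of a year. A baseline difference d thus moves the QALY difference by 0.058·d directly, and further through its correlation with later values, whether or not d is large enough to fire the trigger.

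**The case against.** The strongest objection is scope. The conditional sentence refers back to the multivariate analysis just introduced for cost-effectiveness. On that narrow reading, the margins comparison and the t tests are simply unadjusted and the primary endpoint is untouched by the rule. This stands as a reading, and the text does not settle it. It does not rescue the rule, which is unsound for cost-effectiveness too; and if the other outcomes are unadjusted, hospital is still left out of them.

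A reader might infer that the rule inflates type I error. The documents do not support that: the plan says that imbalance will be corrected, and a mechanically applied trigger is slightly conservative. Inflation needs a choice between results, which the undefined trigger permits but does not prescribe.

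A reader might also infer that a baseline EQ-5D difference biases the QALY comparison. Over repeated randomisations it does not. It adds variance, and it gives an error conditional on the imbalance in one trial. Moreover, the cost-effectiveness analysis is multivariate unconditionally; T = 0 EQ-5D may already be among covariates that the article does not list.

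Finally, the protocol names no prognostic factors and no baseline tests, so the sizes above are illustrations. That is correct. Hospital is the only covariate that the design itself supplies.

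**Conclusion.** The point holds in a limited form. The protocol states an adjustment rule whose model depends on the observed data and whose covariates are chosen by chance imbalance; nothing elsewhere in the document overrides it. This is a badly fixed rule, so it is more than a detail left to an analysis plan. Its scope and its trigger are both unclear.

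The main cost is precision. Under the assumed prognostic strengths, pre-specified adjustment is worth about 3 to 7 power points for the binary endpoint, and the triggered rule recovers less than 1 of them. For continuous outcomes the gain is about 3 to 12 points (90.9 − 79.2 = 11.7 at R² 0.3). The 23% to 40% chance of triggering assumes 5 to 10 independent characteristics tested at 5%. The loss from ignoring hospital depends on how far hospitals differ in outcome, which is unknown. The second cost is a choice between results that should be closed before the data are seen.

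Neither cost invalidates the primary comparison or the sample size. The sentence should nevertheless be changed, because the change is nearly free.

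**What to change.** Delete the conditional sentence and replace it with a fixed rule, applied whatever the observed balance:

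- adjust every between-group comparison for hospital;
- adjust the QALY analysis for T = 0 EQ-5D as well, confirming that it is completed before allocation is known;
- if wanted, add a short named list of factors recorded before randomisation, such as tumour size on pre-operative imaging;
- report the unadjusted results as sensitivity analyses.

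Do not adjust for guidance modality (ultrasound or stereotactic) unless it is fixed before randomisation. The ROLL procedure and WGL procedure sections describe it as part of carrying out the allocated localization, so the arm may influence it, and adjusting could remove part of the treatment effect.

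The cost is wording and slightly more analysis work. If some hospitals recruit few patients, a rule for pooling small sites must be written in advance. Hospital and T = 0 EQ-5D are already recorded, there is no added patient burden for them, and N stays at 316.

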## Discussion

The purpose of the ROLL trial is to compare the standard of care (WGL) with the ROLL procedure on oncological outcome, cost effectiveness, cosmetic outcome, patient comfort and learning curve for the participating physicians.

As published previously by our group, the published studies so far indicate a benefit of the ROLL procedure, but are not conclusive [5]. So far only 1 randomized clinical trial is available, but this trial lacks essential information on tumour free margins and tumour size [16].

A large trial on ROLL published recently including 368 patients showed tumour free margins in 89% of the cases and a 97% identification rate of the sentinel node [17]. These figures are encouraging, but the patients in this study were not randomized, and a hook wire was always inserted at the primary tumour site. In our opinion this will not improve patient comfort and the technique is not easier to perform.

In some studies, patients with non palpable invasive carcinoma, carcinoma in situ and benign lesions were included [18,19]. However, patients with an invasive carcinoma are likely to benefit the most from the ROLL technique. As these patients have to undergo a SNB, they will have to undergo one procedure less, i.e. the placement of a wire.

To the best of our knowledge none of the studies published have evaluated cost-effectiveness. In order to implement the new procedure nationwide, besides oncological outcome the cost-effectiveness should be balanced to make this the new standard of care. Approximately 4.000 out of 13.000 women diagnosed with breast cancer need wire guided localization and a sentinel node procedure. Our hypothesis, based on the current literature, is that 15% (600 patients) less re-operations are necessary after treatment with the ROLL technique. A re-operation costs about € 7000, so eventually € 4.200.000 a year might be saved by this method. Furthermore, abandoning the radiological wire insertion procedure and the shorter surgical operating times could provide an additional cost reduction.

In conclusion, the ROLL trial aims to prove oncological, patient satisfaction and cost effective superiority of the ROLL technique versus the WGL technique in the treatment of patients with a non palpable breast carcinoma.

## Abbreviations

ROLL: Radio guided occult lesion localization; WGL: Wire guided localization; SNB: Sentinel node biopsy; Gr: Grams; HRQOL: Health related quality of life; EQ5D: EuroQuol 5d; EQVAS: EuroQuol visual analogue scale.
